### Study design

2.1

This is a prospective, multicenter cohort study. The study was initiated in July 2019 and will end in December 2021. We plan to recruit 1521 psoriasis vulgaris patients from 14 hospitals in Beijing, Tianjin and Hebei province. All patients will be given therapies based on TCM and Conventional therapy guidelines and then followed-up for 1 year. Prior to recruitment, each participating hospital should be required to obtain ethics approval. Each participating hospital will follow a standard set of procedures. The flow chart of the study is depicted in Figure 1.

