#### Secondary outcomes

2.5.2

(1)Onset time: required time for 75% improvement of PASI scores(2)Maintenance time: the time from improvement (PASI75) to recurrence (PASI50)(3)BSA score: The patient's palm area equivalent to 1% of the BSA(4)Visual analog scale of Psoriasis skin itch score (VAS) score: Urticant degree “0 minutes” represents “do not have urticant feeling”, increase in urticant gradually increased score values. 10 minutes represents “the most serious urticant score”.(5)Skin relapse during treatment and follow-up period: The location of new skin lesions (head/trunk/arm/leg), number (1–2/3–5/6–10/>10) and new attack after 6-month interval (no attack/once, between 2-weeks to 1 month/once, every month to 2 months/once, every 2 to 3 months/once, every 3 to 4 months/once, after more than 5 months).(6)World Health Organization Quality of Life Instruments, which included the 28 items, with full credit of 100(7)Zung self-assessment of Depression, Depression was classified as either mild, moderate or severe.(8)Zung self-rating Anxiety Scale (SAS), Anxiety level was classified as either mild, moderate or severe.(9)The total score of the TCM clinical syndrome scale was calculated using blood heat syndrome, blood dryness syndrome and blood stasis syndrome.(10)Treatment expenses (The cost of registration, TCM, Conventional therapy, examinations, physical therapy, acupuncture, transportation expenses, accommodation, and other expenses)

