#### Non regulatory analysis

2.10.2

For the comparative analysis of 2 groups, qualitative data will be analyzed using the chi-square test, Fisher exact probability, Wilcoxon rank-sum test and CMH chi-square test. Quantitative data in line with normal distribution will be analyzed using *t*-test (homogeneity test of variance between groups, test level at 0.05, and Satterthwaite method will be used for correction when the variance is uneven). Wilcoxon rank-sum test and Wilcoxon signed-rank sum test will be used when the data is abnormally distributed.

The survival analysis will be used to compare statistical significance between the groups (for the appearance of new skin lesions). In addition, the Cox regression model will be used to adjust the impact of baseline PASI values, course of the disease, and body mass index.

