Based on an intelligent and information-based data collection and data management platform, this study observed and followed-up on thousands of patients within a short period. Data will be analyzed after centralized integration to compare conventional therapy with that of the combination of Chinese and Western medicine treatment. Patients will be evaluated based on recurrence rate 6 months after PASI75, onset time, maintenance time, the incidence of new rashes during treatment and follow-up, World Health Organization Quality of Life Instruments/BSA/VAS scores and treatment costs. The long-term efficacy of TCM in treating psoriasis vulgaris through intelligent and information-based data collection and management will then be established and evaluated. It determined the advantages of TCM and provided real-world evidence for the long-term efficacy of TCM for the treatment of psoriasis. In addition, the platform could evaluate the mode and cost-effectiveness of psoriasis vulgaris treatment in the real world. Improvement of skin lesions, patient quality of life, recurrence rates of skin lesions and the state of anxiety and depression will also be able to be evaluated in the future. Long-term follow-ups of patients during remission and recurrence will provide clues to inducing factors and effective interventions for patient treatment. Using the multicenter registration platform to collect large amounts of standardized data within a short period will help mine and analyze long-term efficacy data of TCM for the treatment of psoriasis from the perspective of recurrence.

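### Survival methods are named only for new skin lesions, so onset time, maintenance time and 6-month recurrence after PASI75 have no analysis that handles censoring

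*Protocol article*

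**What the plan says.** All references are to the Protocol article.

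- **Non regulatory analysis** sets tests by type of data. For categorical outcomes, "qualitative data will be analyzed using the chi-square test, Fisher exact probability, Wilcoxon rank-sum test and CMH chi-square test". For continuous ones, "Quantitative data in line with normal distribution will be analyzed using" a t-test, and "Wilcoxon rank-sum test and Wilcoxon signed-rank sum test will be used when the data is abnormally distributed". Survival methods then appear once: "The survival analysis will be used to compare statistical significance between the groups (for the appearance of new skin lesions". The next sentence names no further outcome: "In addition, the Cox regression model will be used to adjust the impact of baseline PASI values, course of the disease, and body mass index".
- **Secondary outcomes** defines onset time as the time needed for a 75% PASI improvement. It also lists "Maintenance time: the time from improvement (PASI75) to recurrence (PASI50".
- **Main outcomes** makes recurrence in 6 months the primary outcome, among patients who first reached PASI75. The **Discussion** places the start of the window: "Patients will be evaluated based on recurrence rate 6 months after PASI75, onset time, maintenance time".
- **Study design**: "All patients will be given therapies based on TCM and Conventional therapy guidelines and then followed-up for 1 year".
- **Sample size calculation** supposes 30% loss to follow-up, and recurrence of 28.6% (integrated) and 20% (TCM).
- **Efficacy analysis** adds logistic regression and propensity score matching. **Missing data analysis** chooses a method according to the judged missingness mechanism. Neither section mentions censoring.

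**The concern.** Maintenance time is observed only in patients who relapse, and onset time only in those who reach PASI75. A t or Wilcoxon test on the observed values leaves out everyone still in remission at the last visit, and those are the patients in whom a treatment that delays recurrence shows its benefit.

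The 6-month recurrence proportion needs six observed months after PASI75 in every responder. Patients lost before then do not have them. If the year of follow-up runs from enrolment, neither do patients who reach PASI75 after month 6. A chi-square test or logistic regression then depends on how those patients are counted, and the plan does not say. The study's stated aim is to show delayed recurrence, so these three outcomes carry its main message.

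**Working it through.** **1. What the primary outcome was designed as.** Take 28.6% versus 20%, two-sided α = 0.05 and power 0.80, with the pooled two-proportion formula:

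n = [1.960·√(2·0.243·0.757) + 0.842·√(0.286·0.714 + 0.20·0.80)]² / 0.086² = 389.3, rounded up to 390.

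This matches the plan's 390 per group. The primary outcome was therefore sized as a fixed-time proportion with complete observation.

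**2. Loss alone, wherever the year starts.** Assume exponential recurrence and exponential independent loss, treat the planning rates as 6-month risks, and let 30% be lost by month 6 after PASI75.

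- Hazards per month: h = −ln(1−p)/6, which is 0.0561 for 28.6% and 0.0372 for 20%. Loss: c = −ln(0.70)/6 = 0.0594.
- Observed recurrences: h/(h+c)·(1 − e^(−6(h+c))). Full window without recurrence: e^(−6(h+c)), which is 0.714·0.70 = 0.500 and 0.80·0.70 = 0.560.
- Lost patients counted as recurrence-free: 24.3% versus 16.9% (difference 7.4 points).
- Patients lost before an event dropped: 0.243/(0.243+0.500) = 32.7% versus 0.169/(0.169+0.560) = 23.2% (difference 9.5 points).
- With loss of 20% in one cohort and 40% in the other, the true 8.6-point difference appears as anything from 4.7 to 12.7 points, depending on which cohort loses more and which counting rule is used.

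**3. Loss plus truncation, if the year starts at enrolment.** Simulation with true 6-month recurrence of 28.6%, 12 months from enrolment, exponential onset and 30% loss by month 12. The onset medians are assumptions; the document gives none.

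| Median onset (months) | Censored = recurrence-free | Dropped if no event and no full window | Responders with 6 full months |
|---|---|---|---|
| 2 | 25.6% | 32% | 76% |
| 3 | 24.8% | 33% | 69% |
| 4 | 24.2% | 34% | 65% |
| 6 | 23.3% | 36% | 59% |

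Analysing only responders with six months of observation time gives about 28.6%, which is unbiased under independent censoring, but it discards 24-41% of responders.

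**4. Maintenance time.** With a common 9-month window after PASI75 (assumed) and no loss, the mean among observed recurrences is 1/h − 9·e^(−9h)/(1 − e^(−9h)).

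- At the 28.6% rate: 17.81 − 13.69 = 4.12 months, with 60% censored. True median ln 2/h = 12.3 months.
- At the 20% rate: 26.89 − 22.64 = 4.25 months, with 72% censored. True median 18.6 months.

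A 6.3-month difference in medians shrinks to 0.13 months in the relapser means. In the model of step 3, the 28.6% rate with 2-month median onset against the 20% rate with 6-month onset gives relapser means of 4.24 versus 3.95 months. The cohort with the longer true maintenance looks worse.

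**The case against.** Several points on the other side stand.

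- **The allocation of tests is inferred.** No sentence assigns a t or Wilcoxon test to onset or maintenance time; this follows from the data-type rule. The reference to new lesions stands in a parenthesis that does not say "only". A fuller analysis plan may go further. Still, the article goes beyond silence: it gives a general rule and names one outcome for survival methods.
- **More than chi-square is planned for recurrence.** Logistic regression, propensity matching and a missing-data section also apply, so a reader should not infer that lost outcomes are ignored. None of these supplies a censoring rule.
- **The clock is open.** The Study design sentence can mean a year after treatment. Anyone reaching PASI75 during treatment would then have the full window, and step 3 would largely fall away. Steps 2 and 4 would not.
- **A 6-month proportion is a legitimate primary outcome**, and it matches the sample size.

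A reader might infer that recurrence will be biased downwards, more so in slower-onset cohorts. The document does not support that. It holds only if censored patients count as recurrence-free. Dropping them biases upwards, and a full-window analysis is unbiased under independent censoring. With one rule applied throughout, a threefold contrast in onset produces a spurious gap of 2.3 points (25.6 − 23.3) under the first rule and about 4 points under the second, against the planned 8.6.

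**Conclusion.** The point holds and should be fixed. It is strongest for onset and maintenance time: they are times to an event, and the tests that the data-type rule gives them use only patients who had the event. For maintenance time this can hide nearly all of a real difference or reverse its order.

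For the primary outcome, the result depends on an unstated choice. The estimate for a true 28.6% ranges from about 23-26% to about 32-36%. This rests on exponential times, independent loss of 30% over 12 months, median onset of 2-6 months and follow-up counted from enrolment. With loss alone (30% by month 6) the two rules give 24.3% and 32.7%. The 30% is a planning figure, not a known loss.

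A reader might go further and call the primary comparison invalid. The document does not support that, because a properly specified full-window proportion would be sound.

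**What to change.** - In Non regulatory analysis, extend the survival methods to onset time and to time from PASI75 to recurrence (maintenance time), censored at the last visit: Kaplan-Meier curves, log-rank tests and the Cox model. State that these replace t and Wilcoxon tests for these outcomes.
- Report the primary outcome as the Kaplan-Meier probability of recurrence 6 months after PASI75, with Cox regression for the adjusted comparison.
- State whether the 1-year follow-up starts at enrolment or after treatment.

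No new outcome and no separate propensity score among responders is needed. The cost is a few sentences and modest programming, with no new data. The downside is the independent-censoring assumption, which should be stated.

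The sample size does not stand in the way. At 28.6% versus 20% the hazard ratio is ln(0.80)/ln(0.714) = 0.662, which needs 186 events (Schoenfeld). If all 507 per group reached PASI75 and 30% were lost by 6 months, about 209 events would be expected, for a power of 0.85. A two-proportion test on the 355 completers per group (507·0.7) would have 0.76. Fewer responders would lower both.

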#### Patient cohort division

2.3.2

Patients received TCM will be classified as the TCM treatment cohort. The TCM treatment course should occupy more than half of the total course of treatment, with the following stratigies:

(1)oral herbal medicine once a day(2)external use of Chinese medicine ointment with the area of body surface area (BSA) greater than or equal to the 10% of patients’ total BSA(3)acupuncture treatment(4)external use of TCM bath.

Patients received Conventional therapy following guidelines will be classified as the Conventional therapy cohort. Conventional therapies includ: external use of drugs (Cuticle promoter and Exfoliator pledge agent, glucocorticoid, vitamin D3, vitamin A acid derivatives, immunomodulatory drugs, and so on), Internal use of drugs (antibiotics, retinoic acid, glucocorticoid and immunosuppressants, biological agents, and so on). The treatment course should occupy more than half of the total course of treatment, with the following strategies:

(1)oral use of chemical drugs(2)external use of chemical drugs ointment with the area of BSA greater than or equal to 10% of the total BSA(3)biological agents injection.

Those who meet the requirements of TCM and Conventional therapy cohort meanwhile will be classified as the integrated therapy cohort.

Study assistants will be responsible for the initial visit and follow-up of each patient. The data collection schedule is shown in Table 1.

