#### Selection of covariates

2.10.4

Covariates will be selected from baseline data or other risk variables affected by treatment. Adjusted analysis will be performed for basic demographic characteristics, body mass index, course of the disease, medical history in the last 3 months, the co-occurrence of psoriatic arthritis, baseline PASI scores, SAS scores, Zung self-assessment of Depression scores, and so on. At the time of patient enrollment to the group. This is to determine if basic conditions between the groups are comparable. Other risk factors will include the use of western medicine (immunosuppressants, biological agents, hormones, antibiotics, and so on).

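### The Cox model for new skin lesions names three covariates, section 2.10.4 names five more baseline items, and the protocol does not say which set governs

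*Protocol article*

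**What the plan says.** The study is observational: "This is a prospective, multicenter cohort study" (section 2.1). Groups follow from the treatment a patient gets, for example "Patients received TCM will be classified as the TCM treatment cohort" (section 2.3.2), with parallel definitions for the conventional and integrated cohorts.

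Section 2.10.2 sets out the time-to-event analysis: "The survival analysis will be used to compare statistical significance between the groups (for the appearance of new skin lesions"). It then names the adjustment: "the Cox regression model will be used to adjust the impact of baseline PASI values, course of the disease, and body mass index". This is the only Cox model in the article, and its list has no open ending.

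Section 2.10.4, on the selection of covariates, gives a longer list. It begins "Adjusted analysis will be performed for basic demographic characteristics, body mass index, course of the disease, medical history in the last 3 months" and continues "the co-occurrence of psoriatic arthritis, baseline PASI scores, SAS scores, Zung self-assessment of Depression scores, and so on". It ties these to the time of enrolment and to checking that the groups are comparable. It then adds: "Other risk factors will include the use of western medicine (immunosuppressants, biological agents, hormones, antibiotics, and so on").

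Section 2.10.5 plans propensity score matching on multiple covariates. It opens with the main efficacy indicators and mentions neither new lesions nor Cox regression.

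**The concern.** Without randomisation, covariate adjustment is the main protection against differences in case mix between the TCM, conventional and integrated cohorts. The protocol names a set of baseline characteristics on which the groups should be comparable, yet the one survival model it specifies uses fewer than half of them.

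Some of the omitted items have a plausible link to both treatment choice and outcome on the protocol's own account. The introduction lists mental stress among the high-risk factors for recurrence, and the anxiety and depression scales are the nearest measures of it. The discussion says that children, elderly, pregnant and breastfeeding patients are enrolled, while the conventional cohort includes retinoids, immunosuppressants and biologics, so age and sex could well influence treatment.

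Two things are at stake. A difference in the new-lesion hazard could partly reflect case mix. And an analyst following 2.10.2 to the letter would report a different hazard ratio from one following 2.10.4, with nothing to settle the choice before the results are seen.

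**Working it through.** **Plan's own figure.** There is none for this model: the article gives no hazard ratio and no number of events for new lesions. The 390 per group in section 2.7 concerns the binary recurrence rate and has no bearing here.

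**Step 1: compare the two lists.**

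| Baseline item | Cox model, 2.10.2 | Adjusted analysis, 2.10.4 |
|---|---|---|
| Baseline PASI | yes | yes |
| Course of disease | yes | yes |
| Body mass index | yes | yes |
| Demographics | no | yes |
| Medical history, last 3 months | no | yes |
| Psoriatic arthritis | no | yes |
| Anxiety score (SAS) | no | yes |
| Depression score | no | yes |

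Counting demographics as one item, 2.10.4 names 8. All 3 Cox covariates are among them, so 8 − 3 = 5 are left out.

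**Step 2: look for a linking statement.** Section 2.10.4 does not say which models its list serves. Section 2.10.5 does not say that the survival analysis is run in the matched sample. Section 2.10.2 refers to neither. The question of which set governs is left open.

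**Step 3: what one omitted factor could do.** For a binary factor that multiplies the hazard by r, with prevalence p1 in one cohort and p0 in the comparator, the hazard ratio is multiplied by about

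B = (1 + p1(r − 1)) / (1 + p0(r − 1)).

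All inputs are assumptions, because the documents give no prevalences and no hazard ratios.

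| p1 (TCM) | p0 (conventional) | r = 1.5 | r = 2.0 |
|---|---|---|---|
| 10% | 30% | 1.05/1.15 = 0.913 | 1.10/1.30 = 0.846 |
| 30% | 10% | 1.15/1.05 = 1.095 | 1.30/1.10 = 1.182 |
| 30% | 30% | 1.000 | 1.000 |

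With milder inputs (r = 1.2, 30% v 20%) the factor is 1.06/1.04 = 1.019. With r = 2.0 and 50% v 20% it is 1.50/1.20 = 1.250.

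The formula treats the omitted factor as independent of PASI, disease course and BMI. If it is correlated with them, the three-covariate model already absorbs part of its effect and B lies nearer 1. The formula also describes the hazard ratio early in follow-up and is approximate later.

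**The case against.** The strongest reply is that 2.10.2 does not say that only these three variables will be used. It precedes a section devoted to covariates, whose list carries no restriction by model or endpoint, and then a section on adjusted analysis with propensity score matching. On that reading 2.10.4 is general and the three variables in 2.10.2 are a brief example. The article is also a condensed account, and the full covariate set for a secondary endpoint is often left to the SAP.

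Much of this stands. A reader might infer from 2.10.2 that the new-lesion comparison is certain to remain confounded. The documents do not support that: nothing excludes the wider list or the matched sample, and bias arises only if an omitted variable both differs between cohorts and predicts new lesions after adjustment for the three. No data on either condition are given.

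A reader might also take this model as the direct evidence on delaying recurrence. It is not. The protocol defines recurrence through PASI (section 2.5.1), measures its delay by maintenance time (section 2.5.2, item 2), and lists new lesions as a separate secondary outcome (item 5) that need not follow remission.

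The appeal to the SAP does not dispose of the point. The article is not silent here: it states one set for this model and a wider one two sections later, without reconciling them.

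**Conclusion.** The point holds as a discrepancy between two adjustment sets, affecting a secondary outcome. Five baseline items named in 2.10.4 are absent from the Cox list in 2.10.2, and no sentence brings them or the propensity score into that model. Read literally, 2.10.2 yields a hazard ratio less protected against case mix than the protocol's own list would allow, so residual confounding is possible but not shown.

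Its size and direction cannot be derived from the documents. The assumed scenarios run from no distortion to roughly 15% downwards or 25% upwards, and nothing indicates which cohort would be favoured. The primary 6-month recurrence comparison is not affected by this point. The change is worth making because it is nearly free and removes a choice that could otherwise be made after the results are known.

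**What to change.** In 2.10.2, state that the Cox model for new skin lesions adjusts for the baseline covariates listed in 2.10.4, or uses the same propensity score as 2.10.5. Two conditions belong in the wording:

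- **Baseline values only.** Anxiety and depression scores are also secondary outcomes, and 2.10.4 allows covariates affected by treatment. Values recorded after treatment starts should not enter this model.
- **No on-study western medicine use.** Section 2.10.4 lists it as a further risk factor, but it overlaps with the definitions of the conventional and integrated cohorts, so adjusting for it would remove part of the contrast being estimated.

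Keep the three-covariate model as a sensitivity analysis. If it is preferred as the main model, give the reason for the narrower set.

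The cost is wording, at least five further parameters, and some loss of patients with missing baseline covariates. With 1521 patients planned, the extra parameters should matter little unless new-lesion events turn out to be few; the article gives no expected number. The data collection schedule is not visible in the text at hand, so confirm that each item is recorded at enrolment.

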#### Missing data analysis

2.10.3

Analysis of the impact of missing data will account for the loss of outcome variables. The data types gathered in this study will include longitudinal data that lists enrollment and completed cases for each center and the reasons for the missing data, as well as determining the distribution of each statistical set. We will then determine the mechanism of deletion, which may include the following 3 situations: complete random deletion, random deletion, and nonrandom deletion. For complete random deletion, the sample mean or general linear model will be used, for random deletion, the traditional regression model will be used, and for nonrandom deletion, the mixed-mode method will be used.

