### Sample size calculation

2.7

The sample size of this study was calculated based on the recurrence rates which is the primary outcome. According to the previous study, taking methotrexate as an example, the recurrence rate of conventional therapies is 73.7%,^[5]^ The recurrence rate of integrated Chinese Medicine is 28.6%,^[20]^ We suppose the recurrence rate of TCM group was 20%. Using non-equality test design by the PASS software, we set the α=0.05 and the power 1-β=0.8, the ratio of cases among each group is 1:1:1, the number of cases calculated is 390 in each group. We suppose a 30% of lost in the follow-up Of the study, the ultimately needed cases in each group is 507.

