Patient management, collection, and analysis of medical data is the aim of the present clinical study. Management of chronic diseases will be investigated using this methodology. Patients will be initially registered using unique codes and then will undergo the relevant examinations based on an standard operation process to ensure consistency. Second, patients will be regularly evaluated for their disease condition by regular follow-up visits. If patients are unable to be physically present, they will be evaluated via online or telephone follow-ups. Third, doctors and patients will have direct access via Wechat IDs managed by research assistants. For common problems, the research assistants will communicate with patients via Wechat to improve patient compliance. Fourth, the database will be regularly checked. Patient treatment plans often change, so it is necessary to review and modify information regularly. Treatments will be evaluated for efficacy and actual benefits of TCM for chronic diseases. After platform establishment, enrollment of patients based on inclusion and exclusion criteria should be strictly followed. Based on preset objectives, there will be different research plans and corresponding statistical analysis required. It will be necessary to hold regular meetings to further develop the platform, share knowledge and data so that investigators can benefit from this platform.

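### The missing-data rule chooses its method by a mechanism that the data cannot settle, and its completely-random branch allows a sample-mean option that misleads if it means filling in values.

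*Protocol article*

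**What the plan says.** Section 2.10.3 of the protocol article (Missing data analysis) concerns missing outcomes: "Analysis of the impact of missing data will account for the loss of outcome variables". Enrolment, completion and reasons for missingness are to be listed by centre. The next step is "We will then determine the mechanism of deletion, which may include the following 3 situations: complete random deletion, random deletion, and nonrandom deletion". Each mechanism has its own method. For the first two: "For complete random deletion, the sample mean or general linear model will be used, for random deletion, the traditional regression model will be used". For the third: "for nonrandom deletion, the mixed-mode method will be used".

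The section fixes no main method ahead of the classification, and it plans no comparison of results across mechanisms. Section 2.7 (Sample size calculation) gives the expected amount of loss: "We suppose a 30% of lost in the follow-up Of the study". The Discussion states that the study is not blinded.

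**The concern.** Two features of the rule look wrong.

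First, the analysis depends on a classification that the data cannot deliver. Whether loss is random or nonrandom turns on the values that were not seen. In an unblinded cohort study, a rule of this kind leaves the choice of method open until the results are visible. It also makes the nonrandom analysis conditional on a finding that no test can produce, so the check most needed at high loss might never be run.

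Second, if the sample mean is put in place of missing outcomes, the filled values carry no new information but are counted as observations. The stake is confidence intervals that are too narrow and P values that are too small or, with a different choice of mean, a diluted treatment difference.

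**Working it through.** **The plan's own figures.** Comparing 28.6% with 20% (section 2.7) at two-sided alpha 0.05 and power 0.80, with pooled variance and no continuity correction, gives 390 per group, as stated. The enrolled number is 390 × 1.3 = 507. At the assumed 30% loss, 507 × 0.7 ≈ 355 per group are observed.

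**Can the mechanism be determined?** Suppose, for illustration, that recurrence is 20% among the 70% of a cohort who are observed. The rate in the whole cohort is then 0.7 × 20% + 0.3 × q, where q is the rate among those lost.
- If q = 20%, the whole-cohort rate is 20%.
- If q = 0%, it is 14%.
- If q = 100%, it is 14% + 30% = 44%.

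The observed data are the same in every case. These are bounds, not forecasts. Baseline covariates and recorded reasons can show that loss is related to something observed, which is evidence against complete randomness. They leave q unidentified, so the step from random to nonrandom remains a judgement.

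**Sample mean read as group-mean filling.** Let n be enrolled per group, m the missing fraction, s the standard deviation, and loss completely random.
- The filled mean equals the observed mean, so its true standard error is √(s² / ((1-m)n)).
- The variance of the filled sample is about (1-m)s², so the reported standard error is √((1-m)s² / n).
- Reported / true = 1-m.
- Type I error = 2 × (1 - Φ(1.96 × (1-m))).

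| Loss m | 1.96 × (1-m) | Type I error |
|---|---|---|
| 10% | 1.764 | 7.8% |
| 20% | 1.568 | 11.7% |
| 30% | 1.372 | 17.0% |

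A simulation with 507 per group, 30% completely random loss, no true difference and 8000 runs gave 16.8%, with a reported-to-true standard error ratio of 0.70. Analysing the observed cases without filling gave 5.1%.

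**Binary recurrence.** If the observed proportion is kept but the chi-square test uses n = 507, the standard error ratio is √0.7 = 0.837. The type I error is then 2 × (1 - Φ(1.96 × 0.837)) = 10.1%. Simulation with 20% recurrence in both groups gave 9.45%. A t-test on the filled values gave 16.4%.

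**Sample mean read as the overall mean.** Filling both groups with the same value leaves type I error near 5% (simulated 5.1%) but multiplies any difference by 1-m. At 30% loss, a true 0.20 SD becomes 0.14 SD.

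**Sample mean read as the mean of observed cases.** Nothing is filled in, and no distortion arises if loss really is completely random.

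**The case against.** The strongest reply is that the text never mentions imputing or substituting. It says only that the sample mean is used, and the items beside it are analysis models. The observed mean is a legitimate estimate under completely random loss, and filling in a mean is an odd idea for a yes/no outcome. This stands, and it is why the numerical part is conditional. Filling in is still a natural reading in a missing-data rule, and nothing excludes it.

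A second reply is that listing reasons by centre makes the first step partly workable. That is true for rejecting complete randomness, so it would be too strong to say that the step cannot be attempted at all. It does not rescue the choice between random and nonrandom loss.

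A third reply is that imputation details belong in a statistical analysis plan that is not shown. The point does not rest on missing detail. The article states a decision rule, and that rule is unsound as written.

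A reader might infer several stronger things that the documents do not support:
- That 17% is the error rate of the plan. It requires the completely-random branch, the sample mean chosen over the general linear model, group-mean filling, an outcome compared as a mean, and 30% missing.
- That the regression model named for random loss is a single regression fill. It may equally be a regression analysis of observed cases.
- That missing PASI is understated because of remote contact. The Discussion says "If patients are unable to be physically present, they will be evaluated via online or telephone follow-ups" but does not say whether PASI is scored there, and the data collection schedule is not reproduced.
- That the missing-data method largely decides the result. No calculation shows this. By the same sample-size formula, the contrasts of 73.7% with 20% and with 28.6% need only 13 and 19 per group.

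**Conclusion.** The point holds in two parts of unequal strength. The firm part is that choosing the method by a determined mechanism cannot be done from the data. It makes the analysis depend on judgement after the fact and leaves the nonrandom analysis optional. This is true however the sample mean is understood, and it matters more because the plan itself expects 30% loss.

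The conditional part is the sample-mean option. Its harm is an inflated error rate under group-mean filling, a 30% dilution of the difference under overall-mean filling, and none if only observed cases are averaged. The figures assume completely random loss, the same missing fraction in both groups, and 30% of outcomes missing, taken from the assumed loss to follow-up. On the only branch where the option is allowed, analysing the observed data without filling already keeps the nominal level, so the option offers nothing in return for the risk.

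**What to change.** Replace the three-way rule in section 2.10.3 with the following:
1. Name one main analysis valid under missing at random for each outcome type, before data are seen. For recurrence this could be a time-to-event analysis with censoring, or multiple imputation. For scores it could be a mixed model or multiple imputation.
2. Always run a sensitivity analysis for nonrandom loss, by pattern-mixture or delta adjustment (tipping point), rather than only when that mechanism is declared.
3. Delete the sample-mean option.
4. Keep the listing of reasons by centre as description and to inform the sensitivity analysis, not to select the method.

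The cost is revised wording and a little programming, with no new data. Where values would have been filled in, confidence intervals will be wider.
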